#### Sample size

Based on preliminary studies, we estimate a between group difference in decline in the number of daily bottles and sippy cups (combined) of 0.7. This equates to a small-moderate standardized effect size (Cohen’s d) of 0.7/2 = 0.35. With *n* = 300 participants (150 per am) the trial will have greater than 85% power to detect an effect size of 0.35 (two-tailed alpha = 0.05)**.** To account for a 20% attrition rate, we will enroll 360 subjects (180 per arm).

Analysis plan: Analyses will be intent-to-treat. Generalized linear mixed models (GLMM) will be employed to analyze primary CRFA outcomes, as well as unique obesogenic and cariogenic outcomes. To test the impact of the intervention on secondary outcomes-- caries, weight for length, velocity of weight gain-- similar GLMM models will be fit. Individuals lost to follow-up at T1 or T2 will remain in the analytic sample. Further details are provided below.

The trial’s primary outcome is frequency of combined sippy cup and bottle use (count/day). The intervention’s effectiveness will be tested by a random-effects Poisson regression model, with the count of bottle/sippy cup as dependent variable, an indicator for study arm, a time indicator and their interaction term as fixed effects, and a random intercept at the person level. We will adjust for child age, given shifts in feeding behavior at this age. If the mean (sd) of the outcome demonstrates over -dispersion relative to a Poisson model, we will use negative binomial regression instead. We will report the coefficient of the interaction term, which estimates the rate ratio in bottle/sippy cup use attributable to the intervention, and its 95% confidence interval. To test the null hypothesis, we will use a z-test.

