To test the impact of the intervention on secondary outcomes (behavioral), we will use random-effect generalized linear regression models. The intervention’s impact will be assessed by the coefficient of the interaction term. The estimate and its 95% confidence interval will be reported. For secondary caries, weight for length, and velocity of weight gain outcomes, logistic regression or a linear regression model will be applied as appropriate. *Anthropometrics*: We will use WHO growth standards [77] to calculate *BMI-for-age Z scores* --weight/length^2^ (kg/m^2^), standardized for sex and actual age at measurement. We will categorize children as “overweight” and “obese” if their BMI-for-age Z-scores exceed + 2 and + 3, respectively, as recommended by the WHO [78], and *Weight velocity Z scores*: for each 6 month period: 6 m. > 12 m. 12 m. > 18 m.

**Missing data** will arise from both non-response and study attrition. Random bias created by missing items will be addressed by using multiple imputations [79]. These will use chained equations incorporating baseline and end-of-study data and behavioral variables. For non-random bias, sensitivity analyses will be used to impute best and worst-case credible values for missing variables and then apply the original analyses to these supplemented data sets.

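### The primary z-test rests on one child-level random intercept with no robust variance stated; if correlation decays between visits, a 6-to-18-month test could run anywhere from below 5% to about 9–10%

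*Protocol article*

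**What the plan says.** The Sample size section of the Protocol article contains the analysis plan. The primary outcome is the daily count of bottles and sippy cups combined, measured at 6, 12 and 18 months. It is modelled by random-effects Poisson regression with arm, a time indicator and their interaction as fixed effects, "and a random intercept at the person level", adjusted for child age. If the counts are over-dispersed, "we will use negative binomial regression instead". The interaction coefficient is reported as a rate ratio with a 95% confidence interval, and the test is stated as: "To test the null hypothesis, we will use a z-test".

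No random slope, serial correlation or robust variance is mentioned. The time term is not defined as categorical, linear or pre/post, and no particular visit contrast is named. For behavioural secondary outcomes the article says only that "we will use random-effect generalized linear regression models", without giving the random-effects structure.

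**The concern.** A single random intercept gives each child one constant shift on the log scale. Dependence between the 6- and 18-month visits is then as strong, on that scale, as between adjacent visits, and all children in an arm share the same trend. The article itself expects feeding to shift at this age. Adjusting for age deals with the average shift, but not with some children weaning faster than others. If they do, counts a year apart will correlate less than counts six months apart.

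The model then fits something close to an average of the three correlations. A model-based standard error for the 6-to-18-month contrast comes out too small, and one for an adjacent-visit contrast too large. At stake are the error rate and the interval coverage of the trial's main result, planned at "two-tailed alpha = 0.05".

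**Working it through.** **1. The plan's own figure.** Inputs from the Sample size section: difference 0.7, divisor 2, 150 per arm, two-sided 5%. Then d = 0.7/2 = 0.35; 0.35 × √(150/2) = 3.03; power = Φ(3.03 − 1.96) = 85.8%. This agrees with the statement that "the trial will have greater than 85% power to detect an effect size of 0.35". The calculation uses no between-visit correlation and no mean count, so it cannot supply the inputs needed below.

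**2. Closed form (equal variances, identity link, three balanced visits).** Let r6 be the correlation of adjacent visits and r12 that of the 6- and 18-month visits. An exchangeable fit uses r̄ = (2·r6 + r12)/3. For the 6-to-18-month contrast, true over assumed variance is R = (1 − r12)/(1 − r̄), and size = 2Φ(−1.96/√R). For example, 0.6 and 0.36 give r̄ = 0.52, R = 0.64/0.48 = 1.333 and size 9.0%.

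| r6 / r12 (assumed) | R | Size, 6 to 18 months |
|---|---|---|
| 0.5 / 0.5 | 1.000 | 5.0% |
| 0.3 / 0.25 | 1.047 | 5.5% |
| 0.5 / 0.4 | 1.125 | 6.5% |
| 0.6 / 0.5 | 1.154 | 6.8% |
| 0.6 / 0.36 | 1.333 | 9.0% |
| 0.6 / 0.3 | 1.400 | 9.8% |
| 0.8 / 0.64 | 1.421 | 10.0% |

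At 0.6/0.36 a 6-to-12-month contrast has size 3.2%, and a single pre/post indicator 7.0%.

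**3. Simulation of the count models.** 150 children per arm, no true effect, random-intercept models fitted by maximum likelihood, model-based z on arm by 18 months, mostly 1,500 or more runs per setting (Monte Carlo error about 0.6 points at 5%). Means and correlations are assumed. Rows with three means use latent correlations in the order 6–12, 12–18, 6–18 months; the other rows show the resulting count correlations as adjacent/12-month.

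| Setting | Poisson | Negative binomial |
|---|---|---|
| Means 3/2.5/2, SD 2, 0.5 throughout (no decay) | 5.0% | – |
| Means 3/2.5/2, SD 2, 0.6/0.6/0.3 | 9.1% | 9.0% |
| Means 4/3/2, SD 2, 0.6/0.6/0.3 | 9.3% | 9.1% |
| Means 3/2.5/2, SD 2, 0.4/0.4/0.15 | 12.0% | 9.8% |
| Rounded normal, mean 2.3, SD 2.1, 0.57/0.33 | 9.5% | 9.0% |
| Poisson-lognormal, mean 1.5, SD 2, 0.45/0.35 | 12.9% | 6.1% |
| Poisson-lognormal, mean 2, SD 2, 0.38/0.30 | 8.5% | 5.3% |
| Poisson-lognormal, mean 3, SD 2, 0.20/0.16 | 6.9% | 5.9% |
| Poisson-lognormal, mean 8, SD 7.0, 0.54/0.36 | 33.3% | 8.1% |
| Rounded normal, mean 4, SD 2, 0.59/0.35 | 1.5% | 1.5% |
| Rounded normal, mean 5, SD 2, 0.69/0.48 | 0.1% | 0.1% |

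At SD 2 and 0.6/0.6/0.3, means 4/3.2/2.5 gave 5.3% and means 5/4/3 gave 4.1%. Repeat Poisson fits of the second row gave 8.9% (1,200 runs) and 8.6% (800 runs); means 4/3/2 with correlations 0.6 and 0.36 gave 8.1% (800 runs).

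The low sizes arise because SD 2 means variance 4. At a mean of 4, Poisson noise alone already accounts for all of it. Positive within-child correlation then leaves less visit-to-visit noise than the model assumes, and the standard error is too large.

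**4. Milder inputs (1,200 runs, Poisson, means 3/2.5/2 unless stated).**
- SD 2, correlations 0.6/0.6/0.5: 4.8%; 0.4/0.4/0.3: 8.1%.
- SD 2, correlations 0.6/0.6/0.3, pre/post indicator: 6.3%.
- If the divisor 2 is the SD of the change and the 12-month correlation is 0.3, the per-visit SD is 2/√(2 × 0.7) = 2/√1.4 = 1.69. Size at 0.6/0.6/0.3 is then 3.9%, or 3.5% at means 4/3/2. With a pre/post indicator it is 2.1%.

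**5. Child-level robust standard errors.** These gave 5.1–5.7% in one set of simulations, covering both the no-decay and the decaying settings, and about 5–6% in five decaying settings of another (800 runs each).

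**The case against.** The strongest reply is that the alarming figures depend on inputs the article does not give. There are no correlations and no mean counts. The effect is a "between group difference in decline in the number of daily bottles and sippy cups (combined) of 0.7", so the 2 it is divided by may well be the SD of the change, and on that reading the inflation disappeared in the settings tried. The 6-to-18-month contrast is also an interpretation: the article speaks of one time indicator and one interaction coefficient. All of this stands, and it rules out any single headline error rate.

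A reader might infer that a useless intervention would be declared effective nearly twice as often as planned. The document does not support that: it describes only the unfavourable end of a range that straddles 5%. A lower 12-month correlation is not enough by itself to produce it.

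A reader might also infer that the negative binomial fallback does nothing. It brought 12.9% down to 6.1% and 33.3% down to 8.1%. It adds visit-level variance but keeps the exchangeable structure, so it helps most where over-dispersion is the main problem and barely helped in other count shapes (9.5% to 9.0%).

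Two further points are fair. With a log link and falling means, the implied correlations of the counts themselves are not exactly equal. And a random-intercept model is a common choice; a z-test is compatible with robust standard errors, which an analysis plan not shown here may specify. That makes the point conditional but does not remove it, because the article does fix the random effects and the test and states no safeguard.

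**Conclusion.** The point holds as a conditional weakness in a stated analysis choice. With model-based standard errors and correlation that falls with time between visits, the size of a 6-to-18-month test is not assured at 5%.

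- **Below 5%:** higher mean counts, under-dispersed counts, or a per-visit SD below 2.
- **About 5–7%:** most mild decay, with one simulated mild case at 8%; about 6–7% for a single pre/post indicator under stronger decay and a per-visit SD near 2.
- **About 9–10%:** per-visit SD about 2, mean counts about 2–3, correlations near 0.6 between adjacent visits and 0.3–0.36 over 12 months.

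The Poisson figures above 10% come from over-dispersed settings in which the plan would switch to negative binomial; there the size was 5.3–9.8%.

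All of this rests on assumed correlations, means and contrast. It is worth correcting because the direction of the error cannot be known in advance and the safeguard is nearly free. Extending it to the secondary outcomes is justified only for repeated behavioural outcomes that turn out to use the same random-intercept structure, which the article does not say.

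**What to change.** In the analysis plan within the Sample size section, keep the model and add one sentence: the z-test and 95% confidence interval for the arm-by-time interaction will use child-clustered (sandwich) standard errors, under both the Poisson and the negative binomial model. Say the same for the repeated behavioural secondary outcomes if they are fitted with only a random intercept. If the full analysis plan already specifies this, no change is needed beyond saying so.

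The cost is one sentence and a software option. No data, participants or change of estimand are involved, and the planned 300 analysed children are ample for a clustered variance. The downside is a somewhat wider interval for the 6-to-18-month effect where correlation decays.

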#### Randomization and masking

Participants will be randomized 1:1 to the intervention or EUC control group, after providing informed consent (see below). Following delivery of the EUC at the T0 (baseline) assessment, the CHW will randomize participants by opening a sealed envelope containing the random assignment (prepared in advance by the project statistician). This sequence preserves masking of outcomes assessment at the T0 interview. Neither the outcomes section of the study database, nor written study materials will include a group identifier, though participants may indicate group assignment to research assistants at the12-month (T1) and 18-month (T2) follow-ups.

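### The power figure is for a difference in means, but the primary test is a Poisson rate-ratio z-test whose standard error can be wrong in either direction, with a remedy for over-dispersion only

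*Protocol article*

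**What the plan says.** The Sample size section of the protocol article bases the trial on a "between group difference in decline in the number of daily bottles and sippy cups (combined) of 0.7". It divides this by 2 to give a standardised effect of 0.35 and claims "greater than 85% power to detect an effect size of 0.35" with 150 per arm and "two-tailed alpha = 0.05".

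The analysis plan under the same heading names the daily count of bottles and sippy cups as the primary outcome. The model is a Poisson regression with arm, time and their interaction as fixed effects, adjustment for child age, and a person-level random intercept. The interaction is reported as a rate ratio with a 95% interval, and the article adds: "To test the null hypothesis, we will use a z-test". On dispersion, it says that if the mean and SD of the outcome show over-dispersion "relative to a Poisson model, we will use negative binomial regression instead".

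No mean daily count appears anywhere. The divisor 2 is not labelled as the SD of the decline or of a single day's count. Nothing is said about variance below the Poisson level.

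**The concern.** Given a child's random intercept, a Poisson model sets the variance of each count equal to its mean. It therefore implies that the variance of a within-child change is at least the sum of the two visit means. Neither the random intercept nor a negative binomial model can represent less, because both only add variance. The natural reading of the 2 is the SD of the decline, since it divides a difference in decline. The variance of change is then 4, which the model can match only if the two visit means sum to no more than about 4 per day. Above that, model-based standard errors are too large, the interval is too wide and power is lost.

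If the within-child variance is larger than the model allows, the error reverses and false positives exceed 5%.

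The dispersion check does not settle which case applies. It uses the raw mean and SD, which mix between-child spread (already carried by the random intercept) with the within-child variation on which the interaction test depends.

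**Working it through.** **Inputs from the article (Sample size; Randomization and masking).** Difference 0.7, divisor 2, two-sided alpha 0.05, 150 per arm, 1:1 allocation.

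**Assumptions, not in the article.** Control means from 3 to 2 up to 6 to 5 per day, with intervention follow-up 0.7 lower; two visits; SD 2 at each visit. Within-child correlation is 0.5, giving a variance of change of 4 + 4 − 2(0.5)(4) = 4 (SD 2), or 0, giving 8.

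**1. The stated power reproduces.** 0.7 / (2 × √(2/150)) = 0.7 / 0.2309 = 3.03. Then 3.03 − 1.96 = 1.07, and Φ(1.07) = 0.858 (0.856 with the t distribution). The figure is right for a comparison of two mean declines.

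**2. The planned test.** With two visits and before age adjustment, the random-intercept Poisson estimate of the interaction is log[(S11/S10)/(S01/S00)], where S is the total count by arm and visit. Its model standard error is √(Σ 1/S). The true variance per arm is approximately (4/m0² + 4/m1² − 2ρ·4/(m0·m1)) / 150.

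**3. One case in full: control 5 to 4, intervention 5 to 3.3, ρ = 0.5.**
- Totals: 750, 600, 750, 495.
- Model SE = √(1/750 + 1/600 + 1/750 + 1/495) = 0.0797.
- True variance: control (0.16 + 0.25 − 0.20)/150 = 0.00140; intervention (0.16 + 0.367 − 0.242)/150 = 0.00190. True SE = √0.00330 = 0.0574.
- The model SE is 0.0797/0.0574 = 1.39 times the true one.
- Log rate ratio = ln(3.3/4) = −0.192. Power = Φ[(0.192 − 1.96 × 0.0797)/0.0574] = Φ(0.63) = 0.74.

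**4. Simulation** (150 per arm, rounded counts floored at zero, several independent runs; ranges show agreement between runs).

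| Control means | Poisson power, SD of change about 2 | Sandwich power, same data | Poisson type I error, SD of change about 2 | Poisson type I error, uncorrelated counts of SD 2 |
|---|---|---|---|---|
| 3 to 2 | 82–83% | 87–88% | about 2% | about 9% |
| 4 to 3 | 77–79% | 90–91% | about 1% | 6–7% |
| 5 to 4 | 68–70% | about 90% | 0.4–0.5% | about 4% |
| 6 to 5 | 57–59% | about 90% | 0.1–0.2% | about 2% |

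Sandwich errors clustered on the child kept the type I error near 5% throughout. A larger control decline loses less: 5 to 3 gives 82% against 92%.

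**5. The raw check cannot discriminate.** In the 3-to-2 setting the raw means (about 3.06 and 2.16) and variances (about 3.64 and 3.10) are practically the same under both correlations. Yet the Poisson type I error is about 2% in one and about 9% in the other. Only the within-child correlation differs, and a mean-and-SD comparison does not see it.

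**The case against.** A reader might infer that the plan's own SD of 2 proves under-dispersion and that the stated power is therefore lost. The article does not support that. The conclusion needs a mean count, which is not given, and it needs the 2 to be the SD of the decline, which is not stated. At low means even the sign is uncertain: at 3 to 2, the formula in step 2 with the SD held at 2 gives a model SE of 0.114 against a true 0.131, and power of 0.94. Simulation with counts floored at zero gives 82–83%.

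The Background says up to 75% of low-income South Asian 15-month-olds still use a bottle. If a quarter of counts were zero, the variance would be at least mean² × 0.25/0.75 = mean²/3, or 5.3 at a mean of 4. That is raw over-dispersion, which the plan does address. But sippy cups are counted too, so the zero fraction is unknown, and raw over-dispersion does not show that within-child variance is high.

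Three further points are fair. Where standard errors are too large, the test is conservative. Where the over-dispersion check fires, negative binomial regression should absorb some of the excess variance; the 9% is for the Poisson test without that switch, which was not simulated. And a Poisson mixed model with this fallback is conventional, with robust errors often left to an analysis plan.

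These points remove any unconditional claim. They do not remove the mismatch between the power calculation and the test, or the one-sided remedy, both of which the article states for its primary outcome.

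**Conclusion.** The concern holds in conditional form. The power above 85% is correct arithmetic for a test the trial does not plan to use, and the article lacks the inputs needed to say what power the planned test has.

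If the SD of the decline is 2, the simulated power of the planned test is a few points below the stated figure at 3 to 2 per day, about 77% at 4 to 3, 69% at 5 to 4 and 59% at 6 to 5. If 2 is instead the SD of a single count with little within-child correlation, the Poisson test is anti-conservative at low means, with a type I error of about 9% at 3 to 2.

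These figures rest on assumed means, two visits rather than the trial's three, no age adjustment and rounded-normal counts. A third visit would shift the numbers but not the mechanism. The point merits a change because the remedy works in both directions and does not depend on which reading is right.

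**What to change.** Keep the log-link rate-ratio model. Take the z-test and 95% interval from sandwich standard errors clustered on the child, whether Poisson or negative binomial is fitted, so that validity does not hinge on the raw mean-and-SD check. State the assumed mean daily count at each visit and whether the 2 is the SD of the decline or of a single count, and restate power for the arm-by-time rate ratio.

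The cost is a few sentences, a software option and one recalculation, with no new data. The downside is slightly wider intervals where the Poisson variance is too small, which is the correction needed in that case.

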#### Common risk factor feeding behaviors

We will use MySmileBuddy (MSB), an iPad based ECC risk assessment and educational tool [66]. MSB was validated in previous research [67]. The MSB guides parents through a modified 24-h dietary recall for their child. We have adapted the MSB to reflect culturally appropriate SA foods and beverages, as well as the types of bottles and cups used for beverages. Participants are cued by queries (e.g., first thing to eat or drink upon waking) and attractive color photographs of food and beverage groupings. Prior to administration, the research assistant will ask whether the prior 24 h represented a ‘usual day.’ If not, participants will conduct a recall for one day earlier. We will conduct a second 24-h recall for a subset of participants.

*Unique risk factors for obesity* (sedentary behavior/screen time) will be assessed through previously validated questionnaire items used in other large studies. *Unique ECC-risk factors* include dental visits and oral hygiene practices. We will assess frequency of tooth brushing, use of toothpaste, and use of tap water using items from a measure developed by the CDC. Dental health utilization will be assessed through questions at T1 and T2.

The RCT’s **secondary aim** is to reduce the velocity of weight gain in months 12–18, and the incidence of oral caries at 18 months. Weight and length data will be collected by research assistants at the T0, T1, and T2 outcomes assessments. Study pediatricians will train research staff in anthropometrics protocol. For length, two supine measures will be taken using infantometers (Seca 417, Brooklyn NY), to the nearest 0.1 cm. For weight, children will be measured with diaper and light clothing. ECC will be assessed by study staff using Intraoral cameras at the 18 month follow-up. Intraoral cameras are valid [68–72] and acceptable [73] in young children. Images will be transmitted to pediatric dentists at the Kodiak who will determine the presence of visible dental caries and (if any) their severity (Table 3).

**Table 3 Tab3:** Common Risk/Health Factor Measures

Construct	Variable Measure	Source
Bottle/Sippy:	Any (Y/N)	24 h recall (MSB)
	Frequency (#/day)	24 h recall (MSB)
	Added sweet/solid (Y/N)	24 h recall (MSB)
	@ Bed or Nap (Y/N)	24 h recall (MSB)
Dietary Pattern	F & V servings (#/day)	24 h recall (MSB)
	Juice & sweet drinks (#/day)	24 h recall (MSB)
	Sweet & salty snack (#/day)	24 h recall (MSB)

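### Dental visits are recorded only after randomisation, so the arm-by-time interaction named as the effect measure does not estimate the intervention effect for this outcome

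*Protocol article*

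**What the plan says.** All references are to the protocol article.

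- **Effect measure.** The analysis plan, under Sample size, states: "To test the impact of the intervention on secondary outcomes (behavioral), we will use random-effect generalized linear regression models". It adds that the intervention's "impact will be assessed by the coefficient of the interaction term". The model containing that term is set out for the primary outcome: study arm, time, their product, and a random intercept per person.
- **Scope.** The overview paragraph of the same section says that generalised linear mixed models "will be employed to analyze primary CRFA outcomes, as well as unique obesogenic and cariogenic outcomes".
- **Dental visits.** Outcomes measurement lists more dental visits among the hypothesised benefits. Table 3 has them as a yes/no item under unique oral health. The Intervention section directs patient navigation at two dental visits during follow-up. On timing, Common risk factor feeding behaviors says: "Dental health utilization will be assessed through questions at T1 and T2".
- **Randomisation.** Under Randomization and masking, allocation takes place at T0, after the baseline assessment.
- **Caries, weight for length and weight velocity.** The overview says of these: "caries, weight for length, velocity of weight gain-- similar GLMM models will be fit". The later, more detailed text says: "For secondary caries, weight for length, and velocity of weight gain outcomes, logistic regression or a linear regression model will be applied as appropriate". Table 2 schedules a single caries examination, at 18 months. Velocity is computed for 6 to 12 and for 12 to 18 months.

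**The concern.** An arm-by-time interaction is a sound effect measure when the reference time precedes randomisation. The arms should then differ only by chance at that time, so the change in the between-arm difference is the treatment effect. If the earliest value is itself post-randomisation, the treatment may already be acting at the reference time, and the interaction subtracts that effect out.

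Dental visits are in this position. An intervention that raised attendance by 12 months and kept it raised to 18 months could be reported as having no impact, because the named coefficient does not look at the sustained part. If the benefit came early and then narrowed, the coefficient would point against the intervention. The article names no other effect measure for this outcome.

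**Working it through.** **The plan's own figure.** The article gives no power figure for dental visits. Its only one, for the primary outcome, reproduces. With d = 0.7/2 = 0.35 and 150 per arm, d × √(150/2) = 0.35 × 8.660 = 3.031. Subtracting 1.960 leaves 1.071, and Φ(1.071) = 85.8% (t-test version 85.6%), against a stated value above 85%. That outcome is measured at T0, so its interaction test is not in question.

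**What the interaction estimates.** Write logit P(visit) = b0 + b1·arm + b2·time + b3·arm·time + person effect.

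- Reference time T0: b1 is the pre-randomisation difference, expected to be zero, so b3 is the effect at follow-up.
- Reference time T1 (dental visits): b1 is the log odds ratio at T1 and b1 + b3 is the log odds ratio at T2. Hence exp(b3) = OR(T2)/OR(T1).

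The second model can be fitted (design rank 4 of 4). It answers a different question.

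**Worked example (all rates assumed).** Control 10% then 20%; intervention 25% then 42.86%.

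- T1: (0.25/0.75)/(0.10/0.90) = 0.3333/0.1111 = 3.00
- T2: (0.4286/0.5714)/(0.20/0.80) = 0.75/0.25 = 3.00
- Interaction ratio: 3.00/3.00 = 1.00

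**Range when the effect is not constant (assumed odds ratios).**

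| OR at T1 | OR at T2 | Interaction ratio |
|---|---|---|
| 2 | 2 | 1.00 |
| 3 | 2 | 0.67 |
| 2 | 3 | 1.50 |

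The intervention helps at both visits in every row, yet the tested quantity is null, adverse or favourable depending only on the trend.

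**Simulation for dental visits.** Inputs: 150 per arm (the article's analysed number). Assumed: constant odds ratio 2; control probabilities 10% and 20% at the centre of the person effect; person-level SD 1 on the logit scale. Logistic GEE with an independence working correlation stood in for the random-intercept model; 500 runs.

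- Interaction test: rejected in 5.0% of runs; mean interaction odds ratio 0.99.
- Between-arm test over T1 and T2: rejected in 81%.

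**Caries and weight velocity, only if the overview's model sentence is taken to carry the interaction test.**

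- Caries, T2 only: time is constant, so its column duplicates the intercept and the product duplicates arm. Design rank is 2 of 4 and the interaction cannot be estimated.
- Velocity, both intervals after randomisation: with an assumed effect of 0.35 SD in each interval and correlation 0.3 (4,000 runs), the interaction rejected in 4.6% and the 12 to 18 month between-arm contrast in 85%.

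Under the detailed text, which gives these outcomes logistic or linear regression, neither problem arises.

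**The case against.** **The interaction rule is limited to behavioural outcomes.** This stands. Because caries has one examination and velocity has no pre-randomisation interval, a reader might infer that the plan tests them with an interaction that is inestimable or uninformative. The text does not support that. The detailed plan gives them a separate rule with no interaction named. The overview sentence names a class of model, comes before the interaction model is defined, and refers the reader to details that follow. For caries, a logistic regression on the single examination is already a natural reading of the plan. For velocity, the stated aim concerns months 12 to 18, which a linear regression on arm can address. What remains is two descriptions that do not match.

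**Dental visits are not expressly labelled as behavioural secondary outcomes.** True: the abstract's list of secondary outcomes omits them, and the overview sentence that covers them names no coefficient. But they sit among the hypothesised behaviour changes and are classed as a unique caries risk factor under the mixed-model sentence. The interaction is the only effect measure named for the primary and behavioural outcomes, so classing them with either leads to the same coefficient.

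**Questionnaires are also given at T0, or T0 could be set to no visits.** Table 2 does list questionnaires at baseline, but the sentence specific to dental utilisation names T1 and T2 only. Setting everyone to zero at T0 would not help: the baseline log-odds would not be finite in either arm, so the logistic interaction would have no finite estimate.

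**The example is a constructed case.** Partly fair. The exact null needs a constant odds ratio. The control rates are assumed and well above the only attendance figure in the article, 1.5% of one-year-olds per year. At that rate about 150 × 0.015 = 2.25 control children per year would have a visit, and a between-arm test would be weak too. The 81% is therefore illustrative. That the interaction equals OR(T2)/OR(T1) does not depend on the rates.

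**Conclusion.** The point holds for dental visits. Both measurements follow randomisation, so the named coefficient measures a change in the arm effect between 12 and 18 months and not the effect. If the odds ratio is constant, its test rejects only at about the 5% type I error rate; if it is not constant, the coefficient still is not the intervention effect. This rests on reading dental visits as covered by the interaction rule, which is the natural reading but not an explicit one.

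For caries and weight velocity there is only an inconsistency between the overview and the detailed text. It is not evidence that the interaction rule applies to them.

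The matter should be corrected before analysis but ranks below an essential fix. The primary outcome, daily bottle and sippy-cup count, is measured at T0, T1 and T2. Neither its test nor the sample size is affected.

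**What to change.** 1. Restrict the interaction test to outcomes measured at T0.
2. For dental visits, state the effect as the between-arm contrast, either at T2 or averaged over T1 and T2, and say in advance which.
3. For caries and weight velocity, align the overview ("weight for length, velocity of weight gain-- similar GLMM models will be fit") with the detailed text ("logistic regression or a linear regression model will be applied as appropriate") and name the arm term as the effect: for caries at the single T2 examination, and for velocity in the interval or intervals to be tested.

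The cost is analysis wording only. No new data, visits or participants are needed.
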